#### Intervention

After enrolment, urologists, sonographers, and radiologists will perform TURP and TPLA according to the treatment allocation.

##### TPLA

The patient will be placed in the lithotomy position on a treatment couch with a three-cavity urethral catheter inserted and will undergo routine disinfection and draping before surgery. The treatment will be performed under local anaesthesia in the perineal region with lidocaine. The optical fibre will be inserted inside the prostate under TRUS guidance (Figure 2). For a prostate volume smaller than 40 ml, two fibres will be used, while four fibres will be used for a prostate volume larger than 40 ml (Figures 3, 4). A safe distance of 8 mm from the fibre to the urethra will be maintained, at least 15 mm from the fibre tip to the bladder neck and 10 mm from the outer edge of the prostate capsule. In the case of two applicators, they must be positioned sequentially at a mutual distance of 8–10 mm. Each treatment will be performed at a fixed power of 3 W. Each ablation time is 600 s to maintain the total energy equal to 1,800 J per fibre. The main goal of the treatment is to deliver 1,800 J of energy for the first ablation; if needed, the pull-backs can deliver a total amount of 1,200–1,800 J, depending on the prostate size. At the end of the treatment, 8 mg of dexamethasone can be administered intravenously for anti-oedema and anti-inflammatory reactions.

**Figure 2 F2:**
[figure not shown]
Patient position and needle positioning. The needle was inserted into prostate under guidance of TRUS and performed oval thermal ablation scope.

**Figure 3 F3:**
[figure not shown]
Planning of the procedure. Two fibres for a prostate volume smaller than 40 ml (one for each side).

**Figure 4 F4:**
[figure not shown]
Planning of the procedure. Four fibres for a prostate volume larger than 40 ml (two for each side).

##### TURP

The patient will be placed in the lithotomy position. After anaesthesia and regular disinfection, 26-F continuous-flow resectoscope with a standard tungsten wire loop (Olympus) will be inserted into the prostate. Images of the bladder and ureterostma will be recorded, and withdraw the resectoscope to the verumontanum to inspect the prostate. The two lateral lobes and the medial lobe of the prostate hyperplasia can be displayed. An Olympus UES-40 SurgMaster (Olympus Europa Holding GmbH) electrical current generator was used with settings of 280 W for cutting and 120 W for coagulation. Both the medial lobe and two lateral lobes of the prostate will be resected. The procedure should be carried out to the bladder neck and not surpassing the verumontanum, after sufficient haemostasis and urethral inspection. The images will be recorded and a three-cavity urethral catheter will be inserted for continuous bladder irrigation.

##### Hospitalisation and Observation

After the treatment, the patients should be closely supervised for 2 days with standard post-operation care and the catheter, in the absence of adverse events, is removed within 2 weeks after the procedure.

### Follow-Up

The efficacy and safety endpoints will be collected 1, 3, 6, 12, and 24 months after the operation, as listed in Table 1.

### Measurements and Clinical Outcomes

#### Data Collection

The measurements and data collection schedule are presented in Table 1.

The general medical history of each patient will be obtained through interviews and a review of existing medical records. The data collected and recorded include demographics (e.g., age, gender, and race/ethnicity) and meaningful past or current illnesses. A history of known drug allergies, other allergies, or a history of allergic reactions and all concomitant medications (including Chinese medicine) will also be recorded.

Vital signs (heart rate, respiration, and blood pressure), electrocardiograph (ECG), amount of bleeding and laboratory tests (liver and kidney function, routine blood tests, and blood electrolytes) will be evaluated before and after the operation within 24 h, and the operation time, treatment time, intraoperative blood loss, and blood transfusion will be recorded as well. The post-operation observation include urine routine, urine flow rate test, IPSS, transabdominal bladder ultrasonography (residual urine measurement), and TRUS, quality of life QoL score, European five-dimensional health scale (EQ-5D) score, sexual function evaluation International Index of Erectile Function-5 (IIEF-5), Male Sexual Health Questionnaire-Ejaculatory Dysfunction (MSHQ-EjD) score. Enhanced magnetic resonance imaging (MRI) will be performed 3 months after treatment.

Regarding quitting patients, the researchers will collect the medical materials integrally and record their quitting reasons and time.

All of the data collectors and evaluators will be blinded to the group assignments. The data in this trial will be collected using electronic case report forms (eCRFs) using a remote data capture (RDC) system (https://clinicaldata.shsmu.edu.cn/). The RDC system will be provided by the Clinical Research Institute of Shanghai Jiao Tong University School of Medicine (Shanghai, China).

#### Adverse Events, Serious Adverse Events, and Safety Measurements

Any clinically significant post-treatment changes determined by the investigator or a designee, including vital signs, ECG, and the safety endpoint within 3 months after surgery should be recorded as AEs.

SAEs include more serious urethral stenosis or urinary incontinence after the operation that results in longer hospitalisation, physical disability or even death.

Any AE or SAE will be monitored and then reported. The severity and causality should also be analysed. The data submitted will be monitored by the Ethics Committee of Shanghai Jiao Tong University Affiliated Sixth People's Hospital and the local ethics committee. Any SAE should be immediately reported to the aforementioned ethics committee.

#### Clinical Outcomes

##### Efficacy Endpoint

The primary efficacy endpoint is the IPSS score change at 3 months from baseline.

The secondary efficacy endpoints include:

IPSS change at 6, 12, and 24 months from baseline.Qmax at 3, 6, 12, and 24 months after treatment.Residual urine volume at 3, 6, 12, and 24 months after treatment.Quality of life score, IIEF-5 score, MSHQ-EjD score (3 item and bother) at 3, 6, 12, and 24 months after treatment.European five-dimensional health scale score EQ-5D at 3 and 6 months after treatment.

##### Safety Endpoint

The safety endpoint is the incidence of complications within 3 months after surgery (hyponatremia, urinary retention, TURS, erectile dysfunction, bladder neck contracture, urethral stricture, perforation of the prostate capsule, infection, sepsis, urinary incontinence, bladder rupture, haematuria, and persistent bacteriuria for more than 3 weeks after surgery), intraoperative blood loss; VAS pain score; postoperative urinary catheter retention time; surgical success rate.

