With the emergence of various intracavitary minimally invasive devices, new technologies are being applied to the medical field, such as transurethral enucleation of the prostate (TUEP), which including plasma kinetic enucleation of the prostate (PKEP), holmium laser enucleation of prostate (HoLEP), thulium laser enucleation of the prostate (ThuleP) and some other laser based methods (22). Lasers show better haemostatic effects and cause less bleeding during operations (23–26). Additionally, lasers are non-conductive; thus, they can be applied in patients with heart pacemakers and other electric implants. Although these new techniques might offer sufficient efficacy and lower risk of complications over standard bipolar-TURP (27, 28), However, the levels of evidence are too low and follow-up still too short to offer solid recommendations, and larger comparative studies are needed to evaluate the ultimate impact of the en-bloc approach on postoperative outcomes (22, 29). And since the surgical approach are transurethral avoiding injury is challenging, and haematuria and urethral stricture may occur after the operation (30–33).

With the guidance of high-frequency transrectal ultrasound (TRUS), which is widely used in the diagnosis and treatment of BPH, the clinician can accurately locate the position of the lesion in the prostate and guide the puncture through the image in real time. The percutaneous transperineal approach occurs distal to the urethra and rectum, to protect these structures and reduce the difficulty of preoperative preparation and operation, and lower postoperative infection effectively (34).

Can laser treatment of prostate guided by TRUS achieve the minimally invasive treatment of BPH using a percutaneous transperineal approach? Researchers have verified transperineal percutaneous laser ablation (TPLA) a feasible and safe method (35–40). Pacella CM conducted a single arm trial, performed the analysis on 160 patients with 6 months follow and 83 patients with 12 months after TPLA (41), and de Rienzo G conducted TPLA for 21 patients, verified the significant advantage in Qmax, IPSS, and peculiar ability to preserve ejaculation (38). However, high-quality RCTs, compared with TURP, the most widely used surgical method and “gold standard” for BPH patients, remained absent. Additionally, the efficacy and safety should be illustrated by a longer follow-up time.

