### Objective and Hypothesis

The primary objective of the study is to assess the efficacy and safety of TPLA vs. TURP in treating BPH. We hypothesise that TPLA has non-inferior efficacy to TURP according to the IPSS score change at 3 months from baseline and lower incidence of post-surgery complications. Secondary endpoints, including the maximum urinary flow rate, patients' quality of Life (QoL) and post-urination residue, operation time and hospitalisation time, will also be assessed.

The secondary objective is to determine the optimal target population in patients with BPH for TPLA treatment.

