#### Statistical Methods

We will report our results according to the CONSORT 2010 Statement (44).

The demographic and clinical characteristics of subjects in TPLA/TURP arms will be described. The qualitative variables will be presented as absolute numbers and proportions. Quantitative variables will be presented as the means ± SD or medians and IQRs as appropriate.

The primary endpoint, the IPSS score change at 3 months from baseline, will be compared using the Mann–Whitney *U*-test or Student's *t*-test as appropriate. The safety endpoint, the incidence of complications within 3 months after surgery, will be compared using the χ^2^ test. The primary analysis will be performed on the ITT set defined as all patients who meet the eligibility criteria and undergo randomisation. Predefined subgroup analysis includes the age group, BPH severity according to the baseline IPSS score, the sites grouped by country. Missing values will be imputed with multiple imputations under the assumption of missing at random except for the safety endpoints. All statistical analyses will be performed using R (version 3.5.1).

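### The complication endpoint is a closed list with a TURP-only item but no rectal, perineal or puncture-tract injury and no category for other events, so the χ² comparison can under-count harms particular to TPLA

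*Protocol article*

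**What the plan says.** The Safety Endpoint section opens: "The safety endpoint is the incidence of complications within 3 months after surgery". A bracket then says what counts: "hyponatremia, urinary retention, TURS, erectile dysfunction, bladder neck contracture, urethral stricture, perforation of the prostate capsule, infection, sepsis, urinary incontinence, bladder rupture, haematuria", followed by a thirteenth item, bacteriuria persisting beyond 3 weeks. Nothing marks these as examples, and there is no residual category. Blood loss, VAS pain, catheter time and surgical success follow as separate safety measures.

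Statistical Methods makes this incidence the tested quantity: "The safety endpoint, the incidence of complications within 3 months after surgery, will be compared using the" χ² test. Under Objective and Hypothesis, the trial hypothesis has two parts, non-inferior IPSS change and "lower incidence of post-surgery complications".

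Three other places bear on the content of the list.

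- The Introduction says of the new route: "The percutaneous transperineal approach occurs distal to the urethra and rectum, to protect these structures".
- The TPLA section sets clearances between the fibre and three structures, namely urethra, bladder neck and capsule edge: "A safe distance of 8 mm from the fibre to the urethra will be maintained, at least 15 mm from the fibre tip to the" (the sentence goes on to name the second and third).
- The adverse-event section casts a wider net than the list: "Any clinically significant post-treatment changes determined by the investigator or a designee" is to be recorded, with severity and causality analysed.

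**The concern.** When an incidence is defined by enumeration, the list decides what the test can see. Here one listed item belongs to the comparator by name. I read TURS as transurethral resection syndrome, since the abbreviation list does not expand it. No listed item corresponds to an injury of the rectum, the perineum or the needle tract, which is the anatomy that the experimental procedure approaches or crosses. The protocol also presents protection of the rectum as an advantage of the route, yet an endpoint with no rectal item cannot test that.

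Fewer complications is half of the stated hypothesis. If the list is followed as written, a TPLA patient whose only complication is, for example, a perineal haematoma counts as free of complications. A favourable safety result would then be open to the reply that part of it comes from the list.

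**Working it through.** **Step 1. What each listed item can capture.**

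| Group | Items |
|---|---|
| Comparator only, by name | TURS |
| Tied to TURP in the Introduction, but at a structure that TPLA could also affect | capsule perforation, urethral stricture |
| Mainly expected with resection, not exclusive to it by wording | hyponatraemia, bladder neck contracture, bladder rupture |
| Possible in either arm | retention, erectile dysfunction, infection, sepsis, incontinence, haematuria, persistent bacteriuria |
| Rectal, perineal or puncture-tract injury | none |
| Other | none |

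The total is 1 + 2 + 3 + 7 = 13 items.

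**Step 2. Omissions that bear on the other arm.** The Abstract names bleeding, and the Introduction secondary haemorrhage, as problems of TURP. The list reaches these only through haematuria, and bleeding that needs transfusion has no item. Ejaculatory dysfunction is absent too, although the Introduction cites a study reporting that TPLA preserves ejaculation. It is measured by MSHQ-EjD as an efficacy score instead. If these events are commoner after TURP, leaving them out lowers the TURP count.

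**Step 3. Whether adverse-event recording closes the gap.** It does for visibility. Table 1 collects adverse events from surgery through 24 months, so a rectal injury would be on file. It does not for the test, because Statistical Methods compares the listed incidence and not the adverse-event rate.

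**Step 4. How much an omission could matter (illustration).** The plan gives no sample size or power for complications. Its 114 patients come from the IPSS calculation.

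Inputs:
- N = 114 / 2 = 57 per arm (Sample Size Calculation, 1:1 allocation).
- TURP incidence 15%, the only rate given (Abstract). It is a general TURP figure, not a rate for these 13 items.
- Assumed: true TPLA incidence also 15%, and all TURP events counted.
- Assumed: a share s of complicated TPLA patients have only unlisted events.

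The counted TPLA incidence is 15% × (1 − s). With x_T and x_P the counts in the TURP and TPLA arms and p̄ = (x_T + x_P)/(2N), the uncorrected χ² test at two-sided 0.05 favours TPLA when

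z = [(x_T − x_P)/N] / √[2p̄(1 − p̄)/N] > 1.96.

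Summing the product of the two binomial probabilities over all such pairs gives:

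| s (assumed) | TPLA patients uncounted, 57 × 15% × s | Counted TPLA incidence | Chance of a significant result favouring TPLA |
|---|---|---|---|
| 0 | 0 | 15% | 2.5% |
| 20% | 1.7 | 12% | 6.7% |
| 33% | 2.8 | 10.05% | 12.0% |
| 50% | 4.3 | 7.5% | 24.2% |

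The calculation is symmetric. If 20% of complicated TURP patients were the ones uncounted, the 6.7% would be the chance of a result favouring TURP. If 20% were uncounted in both arms, the comparison would be 12% against 12%, with about 2.5% on each side.

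**The case against.** A reader might infer that the list is tilted towards TPLA by construction. The document does not support that, for four reasons.

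- Counting genuine TURP harms is not bias. Only uncounted TPLA events could be, and at least seven of the 13 items would register events in either arm.
- The three structures given fibre clearances each have a listed item: urethral stricture, bladder neck contracture and capsule perforation. A prostatic abscess would count as infection. A urethral injury with clinical consequences could appear as stricture, retention, haematuria or incontinence. Only rectal injury or fistula and perineal or puncture-site haematoma clearly lack an item.
- The protocol describes the route as protecting the rectum, not as endangering it, and gives no frequency for any omitted event.
- The omitted bleeding and ejaculatory events may run the other way.

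The assumed shares are also open to challenge. At the upper end, half of all complicated TPLA patients would need to have no listed event at all, which is hard to credit once infection, retention and haematuria count. In addition, a predefined list has a real merit in an open-label trial, because it limits judgement about attribution.

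All of this stands, and it removes any claim about net direction or size. It does not remove the gap itself. It could also be said that a condensed article leaves event definitions to the full protocol. That would explain missing detail, but the bracket here is a stated definition, and followed as written it excludes these events from the test.

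**Conclusion.** The point holds in a limited form. The tested complication endpoint is a closed list that includes a comparator-specific item but has no rectal, perineal or puncture-tract injury and no residual category, so it can under-count harms particular to the transperineal laser route. It also omits bleeding outside haematuria and ejaculatory dysfunction, so the net direction and size of any bias cannot be determined from the document.

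The 7% to 24% range shows only that a few uncounted patients (about 2 to 4 of 57) would be enough to matter. It rests on assumed unlisted shares, an assumed equal true rate, full counting in the TURP arm, and a 15% rate that was not derived for this list. It is not an estimate of the trial's error rate.

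The primary efficacy endpoint and the sample size are unaffected. This is a worthwhile correction, short of one that must be made before the trial can be interpreted.

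**What to change.** Keep the 13 items and add:
- rectal injury or fistula;
- perineal or puncture-site haematoma;
- urethral thermal injury;
- bleeding needing transfusion or intervention;
- ejaculatory dysfunction;
- a category for any other procedure-related complication.

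Apply the extended list identically in both arms. Take events from the adverse-event records already collected, and have the blinded evaluators classify them. State that the χ² test uses the extended incidence, and report each item by arm so that readers can see which ones drive any difference.

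The cost is a change of wording and a few more eCRF categories, with no new visits. There are three drawbacks. The residual category needs some judgement about attribution. Some route-specific events will reveal the arm to the evaluator. The recorded incidence may rise in either arm.

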##### Health Economics Assessment

The comparison of operation time and hospitalisation time are included.

### Statistical Considerations

#### Sample Size Calculation

The sample size is calculated regarding the non-inferiority of efficacy. We assume the mean IPSS changes at 3 months from baseline in the TPLA and TURP groups are the same, the standard deviation of both groups is σ = 6, and the non-inferiority margin is Δ = 3 (10, 34, and 37). With α = 0.05 and β = 0.2, a sample size of 102 is required. Considering a drop-off rate of 10%, the overall sample size is 114.

#### Statistical Methods

We will report our results according to the CONSORT 2010 Statement (44).

The demographic and clinical characteristics of subjects in TPLA/TURP arms will be described. The qualitative variables will be presented as absolute numbers and proportions. Quantitative variables will be presented as the means ± SD or medians and IQRs as appropriate.

The primary endpoint, the IPSS score change at 3 months from baseline, will be compared using the Mann–Whitney *U*-test or Student's *t*-test as appropriate. The safety endpoint, the incidence of complications within 3 months after surgery, will be compared using the χ^2^ test. The primary analysis will be performed on the ITT set defined as all patients who meet the eligibility criteria and undergo randomisation. Predefined subgroup analysis includes the age group, BPH severity according to the baseline IPSS score, the sites grouped by country. Missing values will be imputed with multiple imputations under the assumption of missing at random except for the safety endpoints. All statistical analyses will be performed using R (version 3.5.1).

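### The primary analysis is an ordinary two-group difference test that never uses the non-inferiority margin of 3, so as written it cannot establish the stated hypothesis

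*Protocol article*

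**What the plan says.** Three parts of the protocol article bear on this.

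- **Objective and Hypothesis** (and, in similar terms, the Abstract): "We hypothesise that TPLA has non-inferior efficacy to TURP according to the IPSS score change at 3 months from baseline".
- **Sample Size Calculation**: "The sample size is calculated regarding the non-inferiority of efficacy". The calculation takes equal true mean changes and an SD of 6 in each arm, and it fixes the threshold in IPSS points: "the non-inferiority margin is Δ = 3". It arrives at 102 patients for α = 0.05 and 80% power, raised to 114 to allow for 10% drop-out.
- **Statistical Methods**: "The primary endpoint, the IPSS score change at 3 months from baseline, will be compared using the Mann–Whitney". The alternative offered is Student's t-test, with the choice between the two left open. The next sentence assigns a χ² test to the complication rate in the same style. The primary analysis set is ITT.

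The margin appears only under Sample Size Calculation. Statistical Methods gives no confidence interval for the treatment difference, no null shifted by 3, and no rule for declaring non-inferiority.

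**The concern.** A non-inferiority claim requires rejecting the hypothesis that TPLA is worse than TURP by 3 points or more. A Mann–Whitney or Student's t-test, named without qualification, tests whether the two groups differ at all. There are then only two routes from the named test to a conclusion about the hypothesis.

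1. **A significant result in favour of TPLA.** This would imply non-inferiority, but it is rarely obtained when the treatments are equal, which is the planning assumption.
2. **A non-significant result read as non-inferior.** This is invalid. Failing to detect a difference does not exclude one of 3 points, and the noisier the data, the easier it is to pass.

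The Mann–Whitney option adds a further mismatch. The margin is set on the mean change, while a standard rank test neither estimates a mean difference nor has a null expressed in IPSS points. At stake is the trial's principal conclusion.

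**Working it through.** **Inputs.** From Sample Size Calculation: margin 3, SD 6 in both arms, true difference 0, α = 0.05 (sidedness not stated), power 80%, drop-out 10%. Allocation is 1:1 (Treatment Allocation and Blindness), so 102 evaluable patients means 51 per arm.

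**Step 1: reproduce the stated sample size.** Normal approximation, one-sided 0.05:

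n per arm = 2 × [6 × (1.645 + 0.842) / 3]² = 49.5, rounded up to 50, or 100 in total.

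The noncentral-t version gives 51 per arm, or 102, which is the stated figure. Then 102 / 0.90 = 113.3, rounded up to 114, also as stated. At one-sided 0.025 the results are 63 per arm (126) by the normal formula and 64 per arm (128) by noncentral t, and neither matches. The trial was therefore sized for a one-sided 5% t-test against the margin of 3.

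**Step 2: precision.** SE of the difference = 6 × √(2/51) = 1.188, with 100 degrees of freedom. The half-width of a 90% interval is 1.97 and of a 95% interval 2.36.

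**Step 3: operating characteristics with 51 per arm.** For a true deficit d (TPLA worse by d points), the noncentrality is d / 1.188 for the zero-difference test and (3 − d) / 1.188 for the margin test. At d = 3 the former is 2.525.

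| True deficit of TPLA | Two-sided 5% difference test non-significant | Margin test (one-sided 5%) declares non-inferiority |
|---|---|---|
| 0 | 95.0% | 80.6% |
| 1.5 | 76.0% | 34.8% |
| 2 | 61.5% | 20.9% |
| 3 | 29.4% | 5.0% |
| 4 | 8.5% | 0.7% |

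At d = 0 the difference test is significant in favour of TPLA 2.5% of the time.

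The rows at 3 and 4 are false-claim rates if non-significance is taken as non-inferiority. The rows at 1.5 and 2 lie inside the margin, so they are not errors in that sense, but they show how little a non-significant result says about the size of the deficit.

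**Step 4: the same point on the observed scale.** With an observed SD of 6, the difference test is non-significant whenever the observed difference is within ±2.36. The margin test succeeds only if the observed deficit is below 3 − 1.97 = 1.03. Observed deficits between 1.03 and 2.36 points are thus non-significant and yet fail to show non-inferiority.

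**The case against.** The best defence is that Statistical Methods names only a family of tests and never states a null of zero. A t-test can be run against a null shifted by 3, and a rank test on shifted data. Because 102 is exactly the t-test sample size for the margin, the authors may have had such a test in mind. A journal article is also condensed, and the interval level and decision rule often sit in the full protocol or SAP, which are not shown. Finally, the 29% figure assumes a reading of non-significance that the article does not itself adopt.

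Part of this stands. The data could support a non-inferiority conclusion, so the defect lies in the analysis as described and not in the design. The 29% is conditional on misreading a non-significant p-value. The 5% comparator rests on the inference, from reproducing 102, that α is one-sided.

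The rest does not remove the problem. The article does not leave the primary test to another document: it names one, and an unqualified Mann–Whitney or t-test is conventionally a test of no difference. It is worded just like the χ² test beside it, and nothing elsewhere links it to the margin. An SAP that followed the sentence would inherit the mismatch, and one that used the margin would depart from the published plan.

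**Conclusion.** The concern holds and must be fixed. The primary analysis named in the article does not match the hypothesis or the basis of the sample size. Under the planning assumption of equality, the named test supports a positive conclusion 2.5% of the time, against 80.6% for the margin-based test the trial was sized for. If non-significance is taken as non-inferiority, the false-claim rate at a true deficit of 3 points is about 29%, roughly six times the planned 5% (29.4 / 5.0 = 5.9).

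These figures assume 51 evaluable patients per arm, SD 6, a two-sided 5% t-test for the difference test, and one-sided α = 0.05 for the plan.

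**What to change.** Replace the primary-analysis sentence with wording to this effect:

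- Estimate the difference in mean IPSS change at 3 months, TPLA minus TURP (positive means TPLA is worse), with its confidence interval.
- Declare non-inferiority only if the upper limit lies below 3.
- State the interval level. A two-sided 90% interval (one-sided α = 0.05) matches the 102 evaluable and 114 enrolled patients, with 80.6% power.
- Keep a rank-based shift estimate, with its interval judged against the same margin, as a sensitivity analysis only, so that the choice between tests no longer decides the primary claim.
- If a superiority claim on IPSS is also wanted, test it only after non-inferiority has been shown.

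The cost is one paragraph in the protocol and SAP, with no extra data or patients at the 90% level. If a 95% interval is preferred, power with 51 per arm falls to 70.6%. About 126 to 128 evaluable patients would then be needed, which is 140 to 143 enrolled after 10% drop-out (126 / 0.90 = 140; 128 / 0.90 = 142.2). The level should therefore be fixed before any outcome data are analysed.

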## Discussion

This study is a multicentre randomised clinical trial to assess the efficacy and safety of the novel surgery technique TPLA, which may provide an alternative treatment with lower surgery complications for properly selected BPH patients. With a relatively large sample size, this study intends to achieve internal and external validity at the same time. TRUS-guided TPLA provides a new method for patients with BPH with moderate or severe LUTS. Using very thin applicators and high-precision energy delivery, percutaneous laser ablation has been demonstrated to be safe and effective (45–48). Several preliminary studies including short-term follow-up proved its feasibility, Pacella revealed IPSS improved from 22.5 ± 5.1 to 7.7 ± 3.3 at 6 months and 7.0 ± 2.9 at 12 months, Cai HJ proved ultrasound guided TPLA effective and safe with the QoL improved from 4.9 ± 1.7 to 2.3 ± 1.3 and the Qmax improved from 8.5 ± 3.0 to 15.2 ± 4.8 mL/s at 6 months after the procedure (37, 41). However, no comparison with patients treated with other techniques has been performed, especially TURP, the most widely used surgical method and “gold standard” for BPH patients. This clinical trial will focus on comparing TPLA with TURP, evaluating the results with efficacy, safety index, and health economics assessment.

The use of TRUS guidance with a biplane probe allows repositioning of applicators during the manoeuvre based on the physician experience, and the amount of energy is planned in advance according to the baseline volume of the prostatic lobes (35, 38, 49). The assessment of the extent of the coagulation zone after ablation with transrectal contrast-enhanced ultrasonography is considered a very useful tool for early result assessment (50–52). Therefore, ultrasonography plays an important role in the study. With the monitor of real-time TRUS picture, the laser fibre could be placed precisely in the location and be adjusted dynamically. TRUS guidance contributes to reduce the possibility of urethral injury, and contrast-enhanced ultrasonography after TPLA is helpful to evaluate the dimension and evolution of coagulation, and a supplementary ablation could be conducted if necessary (53).

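### The primary analysis compares 3-month IPSS change without adjusting for baseline IPSS: valid and adequately powered as planned, but it gives up precision that the trial has already collected

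*Protocol article*

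**What the plan says.** The endpoint is defined under Efficacy Endpoint: "The primary efficacy endpoint is the IPSS score change at 3 months from baseline". Statistical Methods then names how it is tested: "The primary endpoint, the IPSS score change at 3 months from baseline, will be compared using the Mann–Whitney" test or Student's t-test, whichever is appropriate. The article names no covariate-adjusted model anywhere.

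Baseline IPSS is measured at screening (Table 1). Under Treatment Allocation and Blindness it is a stratification factor in two bands, 8–19 and 20–35, together with study site. In Statistical Methods it returns only as a subgroup variable.

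The sample size section matches an unadjusted comparison. It supposes no true difference between the arms and a margin of 3 points, and on spread it says that "the standard deviation of both groups is σ = 6". Its conclusion reads: "With α = 0.05 and β = 0.2, a sample size of 102 is required". Allowing for 10% drop-off, the total is 114.

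The only before-and-after spread for IPSS is in the Discussion, from a single-arm TPLA series: "IPSS improved from 22.5 ± 5.1 to 7.7 ± 3.3 at 6 months".

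**The concern.** A test of raw change scores acts as if the regression of follow-up IPSS on baseline IPSS had slope 1. When the true slope is lower, part of the variance of change is baseline variance that a covariate would remove. The arm that happens to start higher will also tend to show a larger fall, whatever the treatment does.

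This matters more than usual here because the conclusion rests on setting a confidence limit against a margin of 3 points. A wider interval than necessary makes non-inferiority harder to show, and a chance baseline difference of a point or so can move the estimate by a visible fraction of that margin. The covariate needed to avoid both is already collected. Because the article names the primary test, this is a stated choice and not a detail left to an analysis plan.

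**Working it through.** **Inputs.** From Sample Size Calculation: true difference 0, SD 6 in both arms (used for the change score), margin 3, α = 0.05, β = 0.2, N = 102. From the Discussion: SD 5.1 at baseline and 3.3 at 6 months. The correlation r between baseline and follow-up IPSS is not given. It is an assumption throughout, shown as a range.

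**1. The plan's own figure.** n per arm = 2(z₀.₉₅ + z₀.₈₀)²σ²/Δ² = 2 × (1.645 + 0.842)² × 36/9 = 49.5, so 50 per arm and 100 in total. With the noncentral t distribution, 50 per arm gives just under 80% and 51 gives 80.6%, hence 102. Then 102/0.9 = 113.3, rounded up to 114. One-sided 0.025 would need 126 (normal) or 128 (t). The stated 102 is therefore a one-sided 0.05 calculation, and it is correct for the unadjusted test.

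**2. Effect of adjustment on precision.**
- Variance of change: s₀² + s₁² − 2r·s₀·s₁
- ANCOVA residual variance: s₁²(1 − r²)
- With s₀ = s₁ the ratio is (1 + r)/2, so the residual SD is 6√((1 + r)/2)

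Results at 51 per arm and one-sided 0.05 (power by noncentral t; N for 80% power by the normal formula):

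| Analysis | Variance ratio | SD | SE of difference, SD√(2/51) | Power | N for 80% power |
|---|---|---|---|---|---|
| Unadjusted | 1.00 | 6.00 | 1.19 | 81% | 100 |
| ANCOVA, r = 0.3 | 0.65 | 4.84 | 0.96 | 93% | 66 |
| ANCOVA, r = 0.5 | 0.75 | 5.20 | 1.03 | 89% | 76 |
| ANCOVA, r = 0.7 | 0.85 | 5.53 | 1.10 | 86% | 86 |

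**3. The same with the cited SDs.** At r = 0.2 the variance of change is 26.01 + 10.89 − 6.73 = 30.17 and the residual variance is 10.89 × 0.96 = 10.45, a ratio of 0.35. At r = 0.6 the figures are 16.70 and 6.97, a ratio of 0.42. A change SD of exactly 6 fits these SDs only at r = (26.01 + 10.89 − 36)/(2 × 5.1 × 3.3) = 0.03, where the ratio is 0.30.

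**4. Baseline imbalance.** In simulation with 102 patients, baseline mean 22.5 and SD 5.1 limited to the range 8–35, the between-arm difference in mean baseline IPSS has these properties:
- no stratification: SD 0.97, and a 30% chance of 1 point or more;
- perfect balance in the two severity bands: SD 0.62, and a 10% chance of 1 point or more.

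Site is also a stratification factor. Nineteen sites by two bands make 38 strata, and 114/38 = 3 patients each, so actual balance probably lies between these two cases.

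Each point of imbalance shifts the change-score difference by (slope − 1), where slope = r·s₁/s₀. That is −0.7 to −0.3 points with equal SDs (r = 0.3 to 0.7), and −1.0 to −0.55 with the cited SDs (r = 0 to 0.7). Against a margin of 3, one point of imbalance is worth between 0.3/3 = 10% and 1.0/3 = 33% of the margin.

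**5. Validity.** In 4,000 simulated trials per scenario (cited SDs, r = 0.03, perfect balance in the severity bands, site ignored), the t-test reported a mean SE of 1.16 while its estimate varied with SD 0.89. Its type I error was 1.8% at a nominal 5%, and its power was 89%. ANCOVA reported 0.65 and varied by 0.65, with type I error 4.8% and power 99.8%. The planned test errs on the conservative side.

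**The case against.** The case for leaving the plan alone is substantial. A t-test of change in a randomised trial is unbiased over repeated randomisation. The sample size was set for exactly this test and reaches its 80%. Randomisation is already stratified by IPSS severity, which cuts the SD of chance imbalance from 0.97 to as little as 0.62. All of this stands. What remains is that the bands are wide, the site strata are thin, and an analysis that ignores a factor used in the allocation overstates its own standard error.

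The size of the gain is also open to challenge. No r is given, and the SDs of 5.1 and 3.3 come from one TPLA series at 6 months, with no TURP arm. For r of 0.2 to 0.6 they imply a change SD of 5.5 to 4.1 and not the planned 6. This limits confidence in the amount, not in the direction.

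A reader might infer more than the documents support:
- *That nothing protects against one arm starting more severe.* The stratification does so in part.
- *That patients end near an IPSS of 7 to 8 wherever they start.* The Discussion gives group means and SDs only.
- *That secondary endpoints are also analysed without baseline.* An entry such as "Qmax at 3, 6, 12, and 24 months after treatment" states a time point, not a method, and Statistical Methods names no test for these endpoints.
- *That the trial is underpowered.* Power of 71% arises only at one-sided 0.025, which is not the level that reproduces 102.

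**Conclusion.** The point holds as one of efficiency and robustness for the primary endpoint only. The planned test is valid, does not inflate the risk of falsely declaring non-inferiority, and meets its stated power at one-sided 0.05. It still discards precision: with equal SDs and a change SD of 6, adjustment would lift power by about 12 percentage points at r = 0.3 and 5 at r = 0.7. The gain would be larger if the SDs resembled the cited series. It also leaves in the estimate a residual imbalance worth 10% to 33% of the margin for each point of baseline difference. The direction is secure whenever the slope of follow-up on baseline differs from 1. The amount depends on an r that the protocol does not give.

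**What to change.** Make the primary analysis an ANCOVA of 3-month IPSS (or of change, which gives the same treatment estimate) on treatment, with continuous baseline IPSS as a covariate. Account for the site stratification factor, for example by country, a grouping that the article already uses for subgroups. Fit the model in each imputed data set, combine by Rubin's rules, and compare the confidence limit of the adjusted mean difference with the margin of 3. The result is in IPSS points, the scale of the margin. The unadjusted comparison can stay as a sensitivity analysis.

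The cost is wording only, best settled before outcomes are seen by arm. Baseline IPSS is already collected, and N stays at 114.
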